## Adverse event management

Adverse events (AEs) are defined as *any untoward medical occurrences in a clinical trial subject that do not necessarily have a causal relationship with the treatment*. All AEs will be listed on the appropriate Case Report Form for routine return to the ‘FIXDT’ central office.

Serious adverse events (SAEs) are defined as any *untoward and unexpected medical occurrence that:*
Results in death;Is life-threatening;Requires hospitalisation or prolongation of existing inpatients’ hospitalisation;Results in persistent or significant disability or incapacity;Is a congenital anomaly or birth defect;Is any other important medical condition that, although not included in the above, may require medical or surgical intervention to prevent one of the outcomes listed.

All SAE will be entered onto the Serious Adverse Event reporting form and faxed to a dedicated fax machine at Warwick Clinical Trials Unit within 24 h of the investigator becoming aware of them. Once received, causality and expectedness will be confirmed by the Chief Investigator. SAEs that are deemed to be unexpected and related to the trial will be notified to the Research Ethics Committee (REC) and sponsor within 15 days. All such events will be reported to the Trial Steering Committee and Data Monitoring Committee at their next meetings.

SAEs that may be expected as part of the surgical interventions, and that do not need to be reported to the main REC, are: complications of anaesthesia or surgery (eg, wound complications, infection, damage to a nerve or blood vessel and thromboembolic events) and secondary operations for or to prevent infection, mal-union, non-union or for symptoms related to the metalwork. All participants experiencing SAEs will be followed-up until the end of the trial, per protocol.

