Only two prospective RCTs have been published to date. In the first, 64 patients were randomised either to intramedullary nail or plate fixation, for the treatment of a closed extra-articular fracture.^12^ The time to union was found to be similar for the two groups, and there was no difference in terms of Olerud and Molander Ankle Score (OMAS) at 2 years. However, a significant difference was observed in the number of wound complications: one in the intramedullary nail group versus seven in the plate group. This paper concludes that intramedullary nailing is the treatment of choice for this injury. However, the method of randomisation was poorly described and so bias in group assignment may have occurred. The study used traditional (non-‘locking’ plates) rather than the newer fixed-angle devices. Furthermore, the study included patients with Tschene classification C2 soft tissue injuries, which may have influenced the results. The second trial randomised 111 patients either to intermedullary nail fixation or ‘locking’ plate fixation.^13^ This trial also showed no difference in the time to union but, 1 year after the injury, there was some evidence of improved American Orthopaedic Foot and Ankle Society functional scores in the nail group. However, this was a single-centre investigation and over 20% of the patients in the trial were lost to follow-up.

In a meta-analysis, Zelle *et al*^14^ reviewed 1125 extra-articular fractures of the distal tibia. They reported that non-union, mal-union and infection rates were similar for patients undergoing intramedullary nailing and plate fixation. It must be noted that none of the studies in the review were RCTs.

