### Risks and benefits

The risks associated with this study are predominantly those associated with the surgery: infection, bleeding and damage to the adjacent structures such as nerves, blood vessels and tendons. Participants in both groups will undergo surgery and will potentially be at risk from any/all of these complications. There are no data to suggest that the risk is greater in one or the other group. We believe that the overall risk profile is similar for the two interventions but assessment of the number of complications in each group is a secondary objective of this trial.

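### The SAE definition requires unexpectedness, which contradicts the rest of its section and leaves expected serious complications without a clear 24-hour report or a stated route to the DMC

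*Protocol article*

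**What the plan says.** All from the protocol article, Adverse event management, unless stated.

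- Adverse events of any kind: "All AEs will be listed on the appropriate Case Report Form for routine return to the" trial's central office.
- Definition of an SAE: an "untoward and unexpected medical occurrence that" meets one of six seriousness criteria, hospitalisation among them.
- Expedited step: "All SAE will be entered onto the Serious Adverse Event reporting form and faxed to a dedicated fax machine at Warwick Clinical Trials Unit", with a limit of 24 hours from the investigator becoming aware.
- Assessment: "Once received, causality and expectedness will be confirmed by the Chief Investigator".
- External notification: SAEs judged both unexpected and trial-related go to the Research Ethics Committee (REC) and sponsor within 15 days. The next sentence reads: "All such events will be reported to the Trial Steering Committee and Data Monitoring Committee at their next meetings".
- Expected events: the section then gives a list introduced as "SAEs that may be expected as part of the surgical interventions, and that do not need to be reported to the main REC". It covers complications of anaesthesia or surgery (wound problems, infection, nerve or vessel damage, thromboembolism) and secondary operations for infection, mal-union, non-union or metalwork symptoms.
- Risks and benefits: "There are no data to suggest that the risk is greater in one or the other group".

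**The concern.** Seriousness and expectedness are separate properties of an event. Seriousness should decide whether a site files an SAE form. Expectedness should decide only who outside the trial must be told quickly. The article puts expectedness into the definition itself and then treats it as something still to be judged.

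This matters because the definition is what a site uses to decide what to fax within 24 hours. With at least 18 centres planned (Trial summary), some could follow the definition and others the list, so SAE counts would not be comparable between sites. The events caught in the contradiction are infection, wound complications and re-operation. The article's own background suggests the two arms may differ on these, so the DMC has most reason to see them. The statement that no data suggest unequal risk makes that need harder to see.

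**Working it through.** The section states no figure to reproduce. The check sets its statements against each other.

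**1. Is the definition consistent with the list?** Let S mean that a seriousness criterion is met and U that the event is unexpected. The definition says SAE = S and U. The list describes events that are SAEs and not U, which is S and U and not U. No event can satisfy that. The list would be empty, and the Chief Investigator's judgement of expectedness could have only one answer. The definition and the procedure cannot both stand.

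**2. What happens to one event?** Take an infection that leads to readmission. It is untoward, meets the hospitalisation criterion and is on the expected list.

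| Step | Site follows the definition | Site follows the list |
|---|---|---|
| Is it an SAE? | No | Yes |
| 24-hour form | No | Yes |
| Chief Investigator assessment | No | Yes |
| Main REC | No | No (stated exemption) |
| Routine adverse event form | Yes | Yes |

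**3. Does it reach the committees?** The sentence sending events to the two committees directly follows the one on unexpected and related SAEs, so *such* most naturally means those. A wider meaning, all SAEs, is possible.

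| | *Such* = unexpected and related | *Such* = all SAEs |
|---|---|---|
| Definition taken literally | Not routed | Not routed (not an SAE) |
| Expected list honoured | Not routed | Routed |

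An expected serious complication has a stated route in one of the four combinations, and that one needs the less natural reading of *such*.

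**4. Is the event lost?** No. All adverse events are returned on case report forms. Outcome measures has all complications and further surgery recorded, and Table 1 collects complications at 6 weeks and 3, 6 and 12 months. The complication rate by treatment is a secondary objective (Objectives).

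**5. Does the risk statement fit the article's own evidence?**

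- Background, a 64-patient randomised trial: "a significant difference was observed in the number of wound complications: one in the intramedullary nail group versus seven in the plate group". Arm sizes are not given. Assuming nail/plate splits of 32/32, 34/30 and 30/34, Fisher's exact test gives p = 0.053, 0.021 and 0.058, and the uncorrected chi-square test gives p = 0.023, 0.014 and 0.037. Whether the result falls below 0.05 depends on the split and the test, but these are data suggesting a difference, and the article itself calls it significant.
- Pre-pilot data, 12 patients per group: more secondary procedures with the plate, no counts given.
- Background, a meta-analysis of 1125 fractures: similar non-union, mal-union and infection rates, with no randomised study included.

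The evidence is mixed. It can support a belief that the overall profiles are similar, but not a statement that no data point either way.

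**The case against.** The strongest reply is that these are wording slips in a condensed article and that safety monitoring works around them. Much of that stands. The events are captured as shown above, and the stated exemption for expected SAEs covers the main REC only. Under Statistical analysis the DMC (expanded there as Data Management Committee, which I take to be the same body) may direct interim analyses. The content of DMC reports is commonly left to a charter or the full protocol, neither of which is shown. It is also conjecture that any site would follow the definition and ignore the list.

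The reply does not remove the contradiction. A charter governs what the DMC receives, not which forms sites file. Routine return of forms is not a 24-hour report, and the power to ask for an analysis is not a stated supply of data.

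A reader might infer three stronger things that the article does not support:

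- *That these complications escape safety oversight altogether.* The capture routes and the DMC's powers contradict this.
- *That the number of missed SAEs can be projected from the 1 versus 7 wound complications.* The article does not say that any of the eight met a seriousness criterion, and non-serious events are not SAEs under any definition. It also notes that the earlier trial used non-locking plates, described its randomisation poorly and included soft tissue injuries that may have affected its results.
- *That participants were told the risks are equal.* The participant information is not shown.

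**Conclusion.** The point holds in a limited form. That the SAE definition contradicts the rest of its section is certain from the text. That expected SAEs lack a stated route to the committees is the natural reading, but it rests on what *such* refers to and on this article alone; an unseen charter may supply the route. The effect is on the promptness and consistency of SAE reporting and on the stated committee route, not on whether complications are recorded or compared. Its size in events cannot be derived from the article. The sentence under Risks and benefits is wrong as written, although the belief in a similar overall risk profile that follows it is defensible. The wording should be corrected. The primary analysis is not affected.

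**What to change.** 1. In the SAE definition, delete the words *and unexpected*, so that seriousness alone triggers the 24-hour form.
2. Keep expectedness, with relatedness, only as the criterion for REC and sponsor notification. The list of expected events then serves its stated purpose.
3. In the committee sentence, replace the opening three words with *All SAEs, expected or not*, and state that the DMC receives them by treatment arm.
4. Reword the sentence under Risks and benefits to acknowledge the wound-complication difference in the earlier randomised trial and the secondary procedures in the pilot, alongside the meta-analysis that found similar rates.

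The cost is a protocol wording change, a clarification to sites and one DMC table. Sites may file somewhat more SAE forms, for events they already record as complications.

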### Risks and benefits

The risks associated with this study are predominantly those associated with the surgery: infection, bleeding and damage to the adjacent structures such as nerves, blood vessels and tendons. Participants in both groups will undergo surgery and will potentially be at risk from any/all of these complications. There are no data to suggest that the risk is greater in one or the other group. We believe that the overall risk profile is similar for the two interventions but assessment of the number of complications in each group is a secondary objective of this trial.

## Data management

The Case Report Forms will be designed by the trial coordinator in conjunction with the trial management team. All electronic patient-identifiable information will be held on a secure, password-protected database accessible only to essential personnel. Paper forms with patient-identifiable information will be held in secure, locked filing cabinets within a restricted area of Warwick Medical School. Patients will be identified by a code number only. Direct access to source data/documents will be required for trial-related monitoring. All paper and electronic data will be retained for at least 5 years after completion of the trial.

## Statistical analysis

It seems likely that some data may not be available due to voluntary withdrawal of patients, lack of completion of individual data items or general loss to follow-up. Where possible, the reasons for data ‘missingness’ will be ascertained and reported. Although missing data are not expected to be a problem for this study, the nature and pattern of the missingness will be carefully considered—including, in particular, whether the data can be treated as missing completely at random (MCAR). If judged appropriate, missing data will be imputed using the multiple imputation facilities (mice package) available in R (http://www.r-project.org/). The resulting imputed data sets will be analysed and reported, together with appropriate sensitivity analyses. Any imputation methods used for scores and other derived variables, will be carefully considered and justified. Reasons for ineligibility, non-compliance, withdrawal or other protocol violations will be stated and any patterns summarised. More formal analysis, for example, using logistic regression with ‘protocol violation’ as a response, may also be appropriate and aid interpretation.

Standard statistical summaries (eg, medians and ranges or means and variances, dependent on the assumed distribution of the outcome) and graphical plots showing correlations, will be presented for the primary outcome measure and all secondary outcome measures. Baseline data will be summarised to check comparability between treatment arms, and to highlight any characteristic differences between those individuals in the study, those ineligible and those eligible but withholding consent.

The main analysis will investigate differences in the primary outcome measure, the DRI at 6 months after surgery, between the two treatment groups on an intention-to-treat basis. In addition, early functional status will also be assessed and reported at 3 months and later functional status at 12 months. The differences between treatment groups will be assessed using a Student t test, based on a normal approximation for the DRI score at 6 months, and at other occasions. Tests will be two sided and considered to provide evidence for a significant difference if p values are <0.05 (5% significance level). Estimates of treatment effects will be presented with 95% CIs.

As discussed earlier, the stratified randomisation procedure will ensure a balance in recruiting centres between test treatments and as we anticipate that any individual surgeon will operate on no more than 2–3 patients enrolled in the trial, we do not expect surgeon-specific effects to be important in this study. However, in addition to the unadjusted analysis (t tests), we will also undertake regression analyses to adjust for any imbalance between test treatment groups in patient age or gender. The fixed effects analysis (linear regression model) will also be generalised by adding a random effect for recruiting centre to allow for possible heterogeneity in patient outcomes due more generally to the recruiting centre. DRI data will be assumed to be normally distributed during modelling, but subsidiary analyses may also be undertaken after appropriate variance-stabilising transformation. The primary focus will be the comparison of the two treatment groups of patients, and this will be reflected in the analysis, which will be reported together with appropriate diagnostic plots that check the underlying model assumptions. Treatment effects will be presented, with appropriate 95% CIs, for both the unadjusted and adjusted analyses.

Temporal patterns of any complications will be presented graphically and, if appropriate, a time-to-event analysis (Kaplan-Meier survival analysis) will be used to assess the overall risk and risk within individual classes of important complications (eg, infection).

A detailed statistical analysis plan (SAP) will be agreed on with the Data Management Committee (DMC) at the start of the study. Any subsequent amendments to this initial SAP will be clearly stated and justified. Interim analyses will be performed only where directed by the DMC. The routine statistical analysis will mainly be carried out using R (http://www.r-project.org/) and S-PLUS (http://www.insightful.com/). Results from this trial will also be compared with results from other trials.

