**Methods and analysis:**

Adult patients presenting at trial centres with an acute fracture of the distal tibia will be considered for inclusion. A total of 320 patients will provide 90% power to detect a difference of 8 points in Disability Rating Index (DRI) score at 6 months at the 5% level. The randomisation sequence is stratified by trial centre and age, and administered via web-based service with 1:1 treatment allocation. Baseline demographic and pre-injury functional data and radiographs will be collected using the DRI, Olerud and Molander, and EuroQol EQ-5D questionnaire. Clinical assessment, early complications and radiographs will be recorded at 6–8 weeks. Functional outcome, health-related quality of life and resource use will be collected at 3, 6 and 12 months postoperatively. The main analysis will investigate differences in DRI 6 months postsurgery, between the two treatment groups, on an intention-to-treat basis. Tests will be two-sided and considered to provide evidence for a significant difference if p values are <0.05.

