### Randomisation

The method of fixation will be allocated using a secure, centralised, web-based randomisation service. The randomisation service will be available 24 h each day to facilitate the inclusion of all eligible patients. The allocated treatment will then be reported to the research associate who will inform the treating surgeon. The surgeon will then arrange the allocated surgery on the next available trauma operating list, as per standard practice at that institution; this will ensure the integrity of the randomisation process. Randomisation will be implemented using a minimisation algorithm (sometimes referred to as *adaptive randomisation*) that attempts, at recruitment of each new patient, to balance the marginal totals for each level of the stratification factors identified below. This is the usual practice for trials run at Warwick clinical trials unit (CTU). Experience indicates that, for studies where some centres recruit only a relative small number of patients, this method tends to perform better than conventional stratification methods.

*Stratification by centre* will help to ensure that any clustering effect related to the centre itself will be equally distributed in the trial arms. The catchment area (the local population served by the hospital) will be similar for all of the hospitals, each hospital being a trauma unit dealing with these fractures on a daily basis. While it is possible that the surgeons at one centre may be more expert in one or the other treatment than those at another centre, all of the recruiting hospitals have been/will be chosen on the basis that both techniques are currently routinely available at the centre, that is, theatre staff and surgeons will already be equally familiar with both forms of fixation. This cannot eliminate the surgeon-specific effect of an individual at any one centre.^22^ However, fixation of a fracture of the tibia is not an uncommon procedure and many surgeons will be involved in the management of this group of patients: between 10 and 30 surgeons at each centre, including Consultants and Trainees. Therefore, we anticipate that each individual surgeon will only operate on 2–3 patients enrolled in the trial, greatly reducing the risk of a surgeon-specific effect on the outcome at any one centre.

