*Stratification on the basis of age* will be used to discriminate between younger patients with normal bone quality sustaining high-energy fractures, and older patients with low-energy (fragility) fractures related to osteoporosis. The stratification will help to identify any effect related to the quality of the patients’ bone. The use of DEXA (dual-energy X-ray absorptiometry) is widely regarded as the gold standard for the assessment of bone density. However, such an investigation may be expensive and not routinely available at all centres.

Therefore, we propose to use age as a surrogate for bone density. In a large study in Norway, involving 7600 participants, it was demonstrated that bone mineral density remains stable up until the age of 50 years. After the age of 50 years, bone mineral density decreased steadily in males, while in females there was an initial decline between the ages of 50 and 65 years, with a further decline in both age groups thereafter.^23^ Over 1000 patients with a fracture were recently assessed in a study by Court-Brown and Caeser.^24^ This study confirmed that there is a clear bimodal distribution according to the age of the patient. The crossover of the two peaks of incidence was around 50 years of age. These studies provide strong evidence that patients over 50 years of age become increasingly vulnerable to fragility fractures. Therefore, we have chosen an age of 50 years as the stratification cut-off for this trial.

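### The leading test of 6-month DRI is an unadjusted t test although allocation is minimised on centre and age; making the already planned adjusted model primary is a free improvement

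*Protocol article*

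**What the plan says.** On allocation, the Randomisation section states: "Randomisation will be implemented using a minimisation algorithm". The algorithm works on the marginal totals of two factors, centre and age, and for age "we have chosen an age of 50 years as the stratification cut-off for this trial". The abstract names the same two factors and a 1:1 ratio.

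On analysis, the Statistical analysis section states: "The main analysis will investigate differences in the primary outcome measure, the DRI at 6 months after surgery, between the two treatment groups", by intention to treat. The method follows: "The differences between treatment groups will be assessed using a Student t test, based on a normal approximation for the DRI score". This covers the 6-month score and the other time points. Tests are two-sided and judged at p<0.05.

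The same section then calls the t tests the unadjusted analysis and says: "in addition to the unadjusted analysis (t tests), we will also undertake regression analyses to adjust for any imbalance between test treatment groups". That sentence goes on to name patient age and gender. The regression is to be generalised with a random effect for recruiting centre, and unadjusted and adjusted effects are both to be reported with 95% CIs. The text does not say that the adjusted result takes precedence.

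**The concern.** A two-sample t test takes its standard error from the total within-arm variance of DRI, including whatever part lies between centres and between age groups. Minimisation keeps the arms alike on those two factors, so that part contributes little to the actual error of the treatment difference. If the factors predict DRI, the t test overstates the error: the p value is too large and the interval too wide.

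The protocol does not treat the factors as irrelevant. It uses age to separate younger patients with high-energy fractures from older patients with fragility fractures. It stratifies by centre because of possible clustering, and it allows for differences in outcome between centres in the additional model.

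What is at stake is the precision of the leading result. Two results are promised for one primary question. If they fall on opposite sides of p=0.05, the one that leads on a natural reading is the one that leaves out the design factors.

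**Working it through.** **Inputs from the protocol (Sample size, Recruitment).** Difference 8 points, SD 20, two-sided 5%, power 90%, 264 analysed (132 per arm), 320 randomised, at least 18 centres.

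**The plan's own figure.** n per arm = 2(1.96 + 1.2816)² × 20²/8² = 2 × 10.507 × 6.25 = 131.3, rounded up to 132, so 264 in total. This matches Table 2.

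**Standard errors.** The t test uses SE = 20 × √(2/132) = 2.46, a 95% CI half-width of 1.96 × 2.46 = 4.83 points. If centre and age explain a share R² of DRI variance and are balanced, the actual SE is 2.46 × √(1−R²).

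**Closed forms (normal approximation, perfect balance).**
- True type I error of the t test: 2[1 − Φ(1.96/√(1−R²))]
- t-test power: Φ((8/2.462 − 1.96)/√(1−R²))
- Adjusted power: Φ(8/(2.462√(1−R²)) − 1.96)

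Example at R² = 0.10, where √0.90 = 0.9487:
- Type I error: 2[1 − Φ(2.066)] = 3.9%
- t-test power: Φ(1.290/0.9487) = Φ(1.359) = 91.3%
- Adjusted power: Φ(3.425 − 1.96) = Φ(1.465) = 92.9%

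| Assumed R² | Type I error, t test | Power, t test | Power, adjusted | CI half-width, t test / adjusted |
|---|---|---|---|---|
| 0 | 5.0% | 90.1% | 90.1% | 4.83 / 4.83 |
| 0.05 | 4.4% | 90.7% | 91.5% | 4.83 / 4.70 |
| 0.10 | 3.9% | 91.3% | 92.9% | 4.83 / 4.58 |
| 0.20 | 2.8% | 92.5% | 95.3% | 4.83 / 4.32 |

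**What such R² values mean.** Assume two age groups of equal size. A 10-point age effect then has variance 10² × 0.25 = 25, or 25/400 = 0.0625 of the total. With a centre ICC of 0.10, R² is about 0.16. With a 5-point age effect (6.25/400 = 0.016) and an ICC of 0.02, R² is about 0.04.

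**Simulation of minimisation.** Assumptions: 18 centres, 40% of patients in one age group, biased coin 0.8, 320 randomised, 264 analysed; 4,000 null and 2,000 alternative trials per scenario. The comparator was ordinary regression with age group and fixed centre indicators.

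| Assumed R² | Type I error, t test / adjusted | Power, t test / adjusted |
|---|---|---|
| 0 | 4.9% / 4.9% | 89.7% / 88.9% |
| 0.05 | 4.4% / 5.0% | 89.9% / 90.7% |
| 0.10 | 4.1% / 4.6% | 90.7% / 92.4% |
| 0.20 | 3.4% / 5.4% | 91.7% / 95.0% |

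Monte Carlo standard errors are about √(0.05 × 0.95/4000) = 0.3 percentage points for type I error and √(0.9 × 0.1/2000) = 0.7 for power. The direction agrees with the closed form. The loss in type I error is a little smaller, as expected when balance is not perfect.

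**The case against.** The strongest reply is that little is at risk. The t test errs on the safe side, the estimate is unbiased, and the adjusted result will be reported with its own 95% CI, so readers will see the narrower interval. The p<0.05 rule is worded for tests in general, and an analysis plan that is not shown may rank the two results. The Randomisation section also gives grounds for modest centre effects: similar catchment areas, both techniques routine at each centre, and 10 to 30 surgeons per centre. All of this stands and limits the severity. It does not remove the point, because the protocol's text attaches the t test to the main comparison and describes the model as an addition.

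Three stronger readings are tempting, and the documents do not support them.
- A reader might infer that the primary test gives too many false positives. The error runs the other way.
- A reader might infer that the trial falls short of its planned power. With 264 analysed at SD 20, t-test power is 90.1% or more in the closed form, and the simulated values are consistent with 90% within Monte Carlo error. What is lost is additional power that the design would have supplied.
- A reader might infer that adjusting for imbalance is a false reason because minimisation has removed it. Gender is not a minimisation factor. If half the patients are women, the difference in proportions between arms has SE √(0.25 × 2/132) = 0.0615, so a gap above 10 percentage points (z = 1.63) occurs in about 10% of trials. Age is balanced only as two bands, and loss to follow-up can disturb balance among those analysed. The stated reason is incomplete, not wrong.

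**Conclusion.** The point holds as a free improvement of moderate to minor severity. The leading standard error, p value and interval leave out the factors that the allocation used. That is conservative whenever centre or age predicts DRI.

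The direction is certain; the size is not. The protocol gives neither an ICC nor an age effect on DRI, so every R² above is an assumption. At 0.05 or below the effect is negligible. At 0.20 the t test's interval is about 12% too wide (4.83/4.32 = 1.12), its type I error is about 2.8%, and 2.8 points of power are forgone (95.3% − 92.5%).

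Two limits apply to the figures. The closed form assumes perfect balance. The simulation used fixed centre effects and no gender term, whereas the planned model has a random centre effect and gender, so the figures show the likely order of gain and are not exact for that model. The simulated row at R² = 0 (88.9% against 89.7%) suggests that adjustment costs at most a little power if the factors do not matter.

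**What to change.** In the Statistical analysis section, name one primary analysis of 6-month DRI: the planned linear model with treatment, age and gender as fixed effects and centre as a random effect. State how age enters. The protocol says only patient age, so the text should commit to at least the under-50/50-and-over grouping used in the minimisation. Take the p<0.05 decision and the leading 95% CI from this model, and keep the t test as a supportive unadjusted summary.

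Say that centre and age are in the model because the allocation used them. Chance imbalance can stay as the reason for including gender.

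The cost is wording in the protocol and the analysis plan. The model is already planned, no new data are needed, and the sample size does not rise. The change should be made before outcomes by arm are seen, so that the choice between the two results cannot appear driven by them.
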